### Procedures

Patients with T2DM will be selected to take part in this study during routine consultations held in an outpatient endocrinology clinic. At the end of the consultation, the endocrinologist, when verifying that the patient meets the inclusion criteria, will ask the patient if they are interested in participating in research on diabetes and melatonin. This question will be followed by reading the informed consent form. All stages of the research will be explained to the patient. This includes the research period, the use of a placebo substance and melatonin, the need to perform capillary blood glucose measurement 6 times a day for 3 days in the first week and 3 days in the third week, the washout period, and the delivery of capillary blood glucose results after the 3 weeks of the project. If the patient agrees to participate in the project, the researcher will ask them to sign the free and informed consent form. A copy of this form will be given to the patient. Next, the researcher will ask the patient to roll a die. Patients who roll a number from 1 to 3 will be in group 1 and will be included in the group that uses the following sequence: bottle 1, washout, bottle 2. Those who roll a number from 4 to 6 will be included in group that uses the following sequence: bottle 2, washout, bottle 1. After allocating the patient to one of the groups, the project researcher will fill in the research record, which will contain the epidemiological, clinical, and laboratory data of the patient, including age, gender, duration of diabetes, history of epilepsy, insulin use (or not), STOP-Bang (snoring, tiredness, observed apnea, high blood pressure, BMI, age, neck circumference, and gender) questionnaire results, weight, height, BMI, abdominal circumference, and glycohemoglobin value. After this step, the patient will be guided on the diet and physical activity regimens to be carried out during the 3 weeks of the project. Patients will be instructed to perform 30 minutes of physical activity 5 times a week during the 3 weeks of the project. After this guidance, patients will receive a glucometer, strips for measuring capillary blood glucose, and lancets to take home. In addition, patients will be given a form to record capillary blood glucose values. At the end of the third week, the patient will return with the blood glucose values.

### Primary and Secondary Outcomes

The primary end point of this study will be the difference in mean variability of the patients’ blood glucose levels between the first and third weeks of the study. The data will be acquired by computing the average of the variance between the total blood glucose levels obtained in these weeks.

As a secondary outcome, we will evaluate the mean disparities in glycemia at each time interval, namely fasting, 2 hours after fasting, before lunch, 2 hours after lunch, before dinner, and 2 hours after dinner. This assessment aims to determine whether the use of melatonin has any discernable impact on blood glucose fluctuation at specific times of the day.

In order to analyze the effect of melatonin after a greater number of days of use, we will perform a specific analysis of the glycemic variability measured on the last day of glycemic measurement in the first and third weeks.

We will also perform a categorical analysis that will take into account the coefficient of variation of blood glucose levels during the use of placebo and during the use of melatonin. We will consider this value to be stable if it is less than 36% and unstable if it is higher than 36%. We will evaluate whether the coefficient of variation was stable or unstable in the week in which melatonin was used.

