**Methods:**

This study will use a crossover, randomized, double-blind, placebo-controlled trial design. Patients with T2DM in group 1 will receive 3 mg of melatonin at 9:00 PM in the first week, undergo a washout period in the second week, and receive a placebo in the third week (melatonin-washout-placebo). Group 2 will be randomized to receive a placebo-washout-melatonin sequence (3 mg). Capillary blood glucose levels will be measured at 6 different times before and after meals during the last 3 days of the first and third weeks. The study aims to compare the mean differences in blood glucose levels and the coefficient of glycemic variability in patients receiving melatonin and placebo during the first and third weeks. After analyzing the initial results, the number of needed patients will be recalculated. If the recalculated number is higher than 30, new participants will be recruited. Thirty patients with T2DM will be randomized into the 2 groups: melatonin-washout-placebo or placebo-washout-melatonin.

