## Methods

### Study Design

This prospective, crossover, double-blind, randomized, placebo-controlled study was approved by the ethics committee of the Federal University of Minas Gerais. The study will be conducted at an endocrinology outpatient clinic run by the research physician (WM) in the city of Belo Horizonte, Brazil. Thirty patients will participate in the initial phase of this work. These patients will be randomized to 2 groups: a placebo-washout-melatonin (3 mg) group, which will receive a placebo for 7 days, followed by 7 days without the study medication (washout period) and 7 days of melatonin (3 mg); and group 2, the melatonin-washout-placebo group, which will receive melatonin (3 mg) for 7 days, followed by 7 days without the study medication (washout period) and 7 days of placebo. When 15 patients are allocated to one of the possible intervention orders (placebo followed by melatonin or melatonin followed by placebo), 15 patients will be allocated to the other, not-yet-complete intervention order. Patients will be instructed to use the study medication at 9:00 PM. Patients will receive guidance on diet and physical activity to be followed during these 3 weeks. On the fifth, sixth, and seventh days of the first week and the fifth, sixth, and seventh days of the third week, the patients will use a glucometer to monitor fasting capillary blood glucose before breakfast, 2 hours after breakfast, before lunch, 2 hours after lunch, before dinner, and 2 hours after dinner. The primary outcome analyzed in this study will be the variability of pre- and postprandial glycemia. The result will be compared between 2 periods: with placebo and with melatonin.

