### Interventions

Patients will use melatonin in the first week and placebo in the third week or placebo in the first week and melatonin in the third week, according to the randomization described. On days 5, 6, and 7 of the first and third weeks of the study, patients will measure fasting capillary blood glucose levels 2 hours after breakfast, before lunch, 2 hours after lunch, before dinner, and 2 hours after dinner. Patients will also receive guidance on diet and physical activity to be followed during these 3 weeks. In the second week, patients will undergo a washout period. At the end of the study, the patients will return to the office with their capillary blood glucose results. At this point, they will be asked whether they experienced excessive daytime sleepiness at any point in the study and whether they suspected at any time whether a substance was the placebo or melatonin.

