### Sample Size

The sample size will be 30 patients. As referenced in the literature, when the SD and population frequencies of a given variable are not known, a pretest should be performed with 30 to 40 patients, and data from this group should be considered a population estimate [24]. After collecting blood glucose data for the first and third weeks, the mean glycemic variability and the SD will be calculated so that the sample size can be recalculated. This is necessary because there are no similar studies in the literature. If the recalculated sample size is less than 30, no new participants will be needed and the study will be concluded. If the new sample size is greater than 30, new patients will be recruited until the new, larger sample size is reached.

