### Statistical Analysis

If quantitative variables adhere to a normal distribution, as represented by the Gaussian curve, their central tendency will be expressed as mean and their dispersion will be quantified by the SD. If the distribution of these variables does not follow a normal distribution, then their central tendency will be described by the median and their dispersion will be characterized by the 25% and 75% quartiles. The Shapiro-Wilk test will be used to assess normality. Categorical variables will be presented using both absolute frequencies and percentages.

Statistical analyses of normal quantitative variables, both before and after the intervention, will be conducted using a paired 1-tailed *t* test. When the distribution is not normal, the Wilcoxon test will be used. The study will have 2 intervention tails: placebo-washout-melatonin and melatonin-washout-placebo. Comparison of blood glucose levels will be performed between the time when the patients used melatonin and the time they used placebo.

The patients will be compared with one another based on the capillary blood glucose results obtained during the first and third weeks.

The epidemiological, clinical, and laboratory data of the patients will be compared between groups 1 and 2 in order to evaluate whether the randomization process has generated groups that lack statistical differences that may influence the research results.

The significance level will be .05 and the software of choice will be SPSS (version 20.0; IBM Corp).

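### The formal primary end point is worded as week 1 versus week 3, which contradicts the melatonin-versus-placebo comparison stated elsewhere and, taken literally, measures only a period effect

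*Protocol article*

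**What the plan says.** All places are in the protocol article.

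**Week wording.** Primary and Secondary Outcomes defines the primary end point as the difference in mean variability of the patients' "blood glucose levels between the first and third weeks of the study". The next sentence describes averaging the variance of the glucose values from those weeks. Neither sentence mentions melatonin or placebo. Statistical Analysis adds: "The patients will be compared with one another based on the capillary blood glucose results obtained during the first and third weeks".

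**Treatment wording.** Study Design names the primary outcome and continues: "The result will be compared between 2 periods: with placebo and with melatonin". Statistical Analysis says: "Comparison of blood glucose levels will be performed between the time when the patients used melatonin and the time they used placebo". The abstract joins the two, giving as an aim the comparison of "the coefficient of glycemic variability in patients receiving melatonin and placebo during the first and third weeks".

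**Test.** Statistical Analysis specifies a paired one-tailed t test at .05, or a Wilcoxon test if the data are not normal. The Figure 2 caption announces unpaired t tests or Wilcoxon tests.

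**Design.** Interventions confirms that both orders are used. Study Design and Randomization close each sequence at 15 patients.

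**The concern.** The end-point definition should fix the primary contrast. Here it fixes a comparison of calendar weeks, in a design where treatment and week are deliberately crossed. Anyone who carried out that sentence as written would average the melatonin effect away and report any drift between weeks 1 and 3 as the result. Drift is conceivable: under Procedures every patient receives diet and exercise guidance at entry, and Limitations accepts that diet and activity may change between the two weeks.

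The analysis section does not clearly overrule the definition. It contains one treatment-based sentence and one week-based sentence that compares patients with each other. The figure caption then names an unpaired test against the paired test in the text. A one-tailed test also needs a sign, and a difference between weeks 1 and 3 has no treatment direction.

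**Working it through.** **Figure to reproduce.** There is none. Sample Size takes 30 from a pretest convention and states no effect size, SD or power. The check is therefore algebraic, with an illustration on assumed effects.

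**Inputs from the article.** Two sequences with n1 = 15 (melatonin first) and n2 = 15 (placebo first); paired t test, one-tailed, alpha .05; all 30 completed (Results).

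**Assumptions.** tau is the melatonin effect (negative is a reduction) and pi is the period effect (week 1 minus week 3). Both are in units of the SD of the within-patient difference. There is no carryover.

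**Step 1: literal week contrast.** The expected week 1 minus week 3 difference is

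- melatonin first: pi + tau
- placebo first: pi - tau
- pooled: pi + tau × (n1 - n2)/(n1 + n2) = pi + tau × (15 - 15)/30 = pi

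The melatonin effect has weight zero whatever its size. If later recruitment left the sequences at, say, 20 and 15, the weight would be 5/35 = 0.14.

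**Step 2: treatment contrast.** The pooled within-patient melatonin-minus-placebo difference has expectation tau + pi × (15 - 15)/30 = tau.

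**Step 3: illustration.** 100,000 simulated trials per row, 15/15, normal differences, paired t test, one-sided .05 in the lower tail:

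| tau | pi | Week 1 - week 3 rejects | Melatonin - placebo rejects |
|---|---|---|---|
| 0 | 0 | 5.0% | 4.9% |
| -0.5 | 0 | 3.3% | 84.9% |
| -0.8 | 0 | 1.8% | 99.6% |
| 0 | -0.5 | 85.0% | 3.3% |
| 0 | +0.5 | 0.0% | 3.3% |

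The 84.9% agrees with the noncentral t calculation (noncentrality 0.5 × √30 = 2.74, power 0.848). For an assumed effect of 0.3 SD, the same calculation gives the treatment contrast a power of 0.484.

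The week contrast falls below 5% when tau is not zero because the opposite-signed effects add only spread: the SD rises to about √(1 + 0.25) = 1.12 for a 0.5 SD effect. With two-sided tests, the second row becomes 2.9% against 75.4%. A 0.5 SD period shift in either direction makes the week contrast reject in about 76%.

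**Step 4: another possible reading.** If each patient's week 1 minus week 3 difference were compared between the two sequences, the expectation would be (pi + tau) - (pi - tau) = 2 tau, free of the period effect. Its standard error is √(1/15 + 1/15) = √(2/15). The noncentrality per unit of tau is 2/√(2/15) = √30 = 5.48, the same as for the paired treatment test. This would be a valid analysis.

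**The case against.** The strongest reply is that the week wording is shorthand. Weeks 1 and 3 are the only weeks with glucose measurement, so naming them may simply label the two measurement periods. Three sections state the treatment contrast. Later paragraphs of Primary and Secondary Outcomes point the same way: the last-day analysis is meant to show the effect of melatonin yet is described by first and third week, and the categorical analysis names placebo and melatonin. Under Blinding, the bottle code is opened after the statistical analysis, which has little purpose if calendar weeks are compared. The sentence comparing patients with one another and the unpaired test in the figure caption could even mean the valid between-sequence analysis of Step 4.

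Most of this stands. A reader might infer from the end-point sentence that the trial is settled on testing a period effect; the article does not support that, because cancellation requires carrying out that sentence literally, pooled over both sequences, against the other statements. The Step 4 reading, however, is nowhere spelled out and does not fit the paired test in the text.

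A reader might also infer that the sample-size recalculation used the wrong mean and SD. Sample Size says only "After collecting blood glucose data for the first and third weeks", which describes timing, and then names mean glycemic variability and its SD. Results is worded similarly. Neither shows that a week 1 minus week 3 difference was used.

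The reply does not remove the contradiction. The section that formally defines the end point gives the version that does not answer the trial's question, and the analysis section leaves more than one contrast open.

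**Conclusion.** The point holds as an internal contradiction in the primary contrast, with the formal definition being the wrong version. It does not hold as proof that a period test was planned or that the recalculation went wrong.

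The cancellation is exact for a pooled 15/15 sample and rests on no assumed effect size. The rejection rates are illustrations only. They apply under the literal reading, with normally distributed differences and assumed effects. The 85% false rejection also needs a 0.5 SD period shift in the tested direction; a shift the other way would almost never reject one-sided. The article gives no evidence on the size of any shift. Because the sentence concerned defines the primary end point, it should be corrected even though the intended comparison can probably be guessed.

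**What to change.** 1. In Primary and Secondary Outcomes, restate the primary end point as the within-patient difference, melatonin week minus placebo week, in the chosen variability measure. State the sign that counts as benefit for the one-tailed test. Analysts who see only bottle numbers can compute the bottle difference and attach the sign when the code is opened.
2. In Statistical Analysis, align the sentence comparing patients with one another to this contrast or remove it. If a between-sequence comparison of within-patient differences was meant, say so explicitly.
3. Reconcile the unpaired test in the Figure 2 caption with the paired test in the text.
4. In Sample Size, state that the recalculation uses the mean and SD of this same within-patient difference. This is a clarification, not the correction of a demonstrated error.

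The cost is wording only. The glucose data already collected contain everything the restated end point needs.

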### Glycemic Variability

Glycemic variability refers to fluctuations in blood glucose levels over time. It can be short-term, in self-monitored evaluations of (pre- and postprandial) capillary blood glucose; it can also use the gold standard method, continuous blood glucose monitoring, in which nocturnal blood glucose fluctuations are recorded every 5 minutes [21,22]. There is little correlation between the average variability in glycemic amplitude measured by continuous glucose monitoring and by self-monitoring; however, the latter method can be used for structured assessments of short-term glycemic variability in a day and between different days. The calculation of glycemic variability by this method can also be performed using SDs or even the coefficient of variation. A glycemic variation coefficient of less than 36% is considered level E evidence to separate stable from unstable glycemic control [21]. This measure is considered most effective to assess glycemic variability; however, comparing glycemia between different days is more effective with the mean of daily differences (MODD). This measure is obtained by determining the difference in blood glucose measured at the same time in a 24-hour interval. An additional computer program is used for this measurement, and it cannot be obtained only by continuous capillary blood glucose monitoring devices [21]. In this work, we will use pre- and postprandial capillary glycemia monitoring to determine the glycemic variability of patients with T2DM. In addition to the low cost of the method, we believe that this method gives the work an aspect of a real-life study and therefore greater clinical relevance.

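### The only described analysis of the coefficient of variation (CV) is a split at 36%, which is noisy at 18 readings and loses power against the continuous CV; a minor point, as the primary end point is not split

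*Protocol article*

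**What the plan says.** Under Primary and Secondary Outcomes, after the primary and secondary outcomes, the article adds: "We will also perform a categorical analysis that will take into account the coefficient of variation of blood glucose levels" under placebo and under melatonin. The rule is "We will consider this value to be stable if it is less than 36% and unstable if it is higher than 36" per cent, and the stated evaluation is whether the CV was stable or unstable in the melatonin week. The Glycemic Variability section gives the source of the cut: "A glycemic variation coefficient of less than 36% is considered level E evidence to separate stable from unstable glycemic control".

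Procedures fixes the data behind each label: "capillary blood glucose measurement 6 times a day for 3 days in the first week and 3 days in the third week".

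Two other statements set the context. The primary outcome is not split: "The primary end point of this study will be the difference in mean variability of the patients’ blood glucose levels" between the two weeks, computed from variances. The Methods paragraph of the abstract says that the study aims to "compare the mean differences in blood glucose levels and the coefficient of glycemic variability in patients receiving melatonin and placebo", and mentions no cut. The Statistical Analysis section gives a one-tailed paired t test, or a Wilcoxon test, for quantitative variables. For categorical variables it gives frequencies and percentages, and it names no test for paired categories.

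**The concern.** A CV computed from 18 self-measured values is an imprecise estimate. Cutting it at a fixed value does two separate kinds of damage. First, a patient near the cut can be stable in one week and unstable in the other with no change in true variability. Second, the label discards how far the CV moved: a real fall that does not cross 36% counts as no change, and a trivial one that does cross counts as a full response.

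The abstract names a comparison of the CV between treatments as an aim, but the outcomes section carries it out only through the label. The primary end point does not fill the gap. It is described as a variance, which is not scaled to mean glucose as the CV is.

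**Working it through.** **Inputs from the article.** Cut 36% (Primary and Secondary Outcomes). Readings per treatment week: 6 × 3 = 18 (Procedures). Patients: 30, each in both periods (Sample Size). Significance level .05, one-tailed for quantitative variables (Statistical Analysis).

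**Inputs not in the article, assumed here.** Mean true CV of 25%, 30% or 36%; between-patient SD of true CV 5 or 8 points; relative fall under melatonin 10% or 15%; independent readings with sampling noise only. The sample size of 30 is a pretest rule with no effect size, SD or power, so there is no figure of the plan's own to reproduce.

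**Sampling SD of one CV, n = 18, true CV 36%.**
- Simple formula, CV/√(2(n−1)): 0.36/√34 = 0.062, or 6.2 points.
- Delta method, CV × √(1/(2(n−1)) + CV²/n): 0.36 × √(0.0294 + 0.0072) = 0.069, or 6.9 points.
- Simulation with normal or lognormal readings: 6.9 to 7.0 points.
- Sensitivity: a fixed meal-time pattern explaining 30% to 70% of the variance gives 6.5 down to 4.8 points; a shared day effect of 20% to 40% gives 7.8 to 9.3.

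**Chance label change with no effect.** If p is the probability that the observed CV exceeds 36%, the two weeks disagree with probability 2p(1−p). With 40% of the variance from a fixed daily profile:
- True CV 30%: p = 0.12, so 2 × 0.12 × 0.88 = 0.21.
- True CV 33%: p = 0.29, so 2 × 0.29 × 0.71 = 0.41.
- True CV 36%: p = 0.49, so 2 × 0.49 × 0.51 = 0.50.

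Across the variants run, the rates are 20–23% at 30%, 37–41% at 33% and 48–50% at 36%. They fall to about 2% at 25% and 0% at 20%.

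**Power, 30 paired patients, one-sided .05.** The paired t test on the continuous CV is compared with McNemar tests on the labels. Ranges cover the two between-patient SDs.

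| Relative fall | Test | Mean CV 25% | Mean CV 30% | Mean CV 36% |
|---|---|---|---|---|
| 15% | Continuous CV | 93–96% | 93–96% | 93–96% |
| 15% | Labels, exact | 2–9% | 33% | 51–62% |
| 15% | Labels, asymptotic | 19–35% | 51–54% | 67–75% |
| 10% | Continuous CV | 63–69% | 63–69% | 63–69% |
| 10% | Labels, exact | 1–5% | 17–18% | 26–33% |
| 10% | Labels, asymptotic | 13–21% | 31–34% | 39–45% |

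Share of power lost for the 15% fall with the exact test, taking the outer bounds:
- Mean CV 36%: 1 − 62/93 = 33% to 1 − 51/96 = 47%.
- Mean CV 30%: 1 − 33/93 = 65% to 1 − 33/96 = 66%.
- Mean CV 25%: 1 − 9/93 = 90% to 1 − 2/96 = 98%.

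For the 10% fall at a mean of 36%, the exact test loses 1 − 33/63 = 48% to 1 − 26/69 = 62%. With the asymptotic test and the 15% fall, the loss is 1 − 75/93 = 19% to 1 − 67/96 = 30% at 36%, and 1 − 35/93 = 62% to 1 − 19/96 = 80% at 25%.

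**The case against.** The strongest case against the point is that a continuous comparison is largely planned already. The primary end point is continuous, the abstract states an unsplit comparison of the CV, and the Statistical Analysis section supplies a paired test for quantitative variables. The split is introduced as an addition and uses a published threshold. No test on the labels is named, so they may be meant only as counts and percentages. This stands, and it limits the point to a minor one. What remains is that the outcomes section describes no CV analysis other than the label, so the abstract's aim is not carried through.

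Three stronger readings are tempting, and the documents support none of them.
- A reader might infer that most of the power is lost. That depends on where patients' CVs lie, the size of the effect and the test used, and the article gives none of these. It holds for CVs averaging about 25%, and at 30% with the exact test. It generally does not hold when they centre on 36%.
- A reader might infer that chance label changes cause the loss. The two harms peak in different places: label changes are commonest at the cut, where the split loses least, and the loss is greatest well below the cut, where labels rarely change.
- A reader might infer that chance changes would imitate a benefit of melatonin. In a paired comparison with no effect they are symmetric, so they add noise and favour neither treatment.

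It is also fair to say that 93–96% power for the continuous CV is a favourable case. The Limitations section expects diet and activity to differ between weeks 1 and 3, and such variation would lower it. The split still lost power against the continuous test when extra week-to-week variation was added.

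**Conclusion.** The point holds as a minor improvement. At 18 readings a CV near 36% has a sampling SD of about 6 to 7 points if readings are roughly independent, and about 5 to 9 points across the meal-pattern and day-effect variants. An unchanged patient would switch label by chance in up to about half of week pairs, but only if the true CV is near the cut. The split also lost power in every case run. The size of the loss cannot be fixed from the article. For 30 patients, a 15% relative fall and an exact paired test, it is from about one third to nearly all of the power, depending on whether CVs centre on 36% or 25%. The primary end point is untouched.

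**What to change.** In Primary and Secondary Outcomes, state that the CV will be analysed as a within-patient melatonin-minus-placebo difference, on the raw or log scale. Use the paired test already given under Statistical Analysis and report a 95% confidence interval. This carries out the aim stated in the abstract. Report the number of patients below 36% in both the placebo and the melatonin week, as description only.

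The cost is about one sentence of text. It needs no new readings and adds no burden for patients. The downside is that the stable/unstable split would no longer be a tested result.
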